## Abstract

**Background:**

Approximately onethird of cancer survivors encounter challenges reintegrating into the workforce, often experiencing involuntary unemployment and/or partial or full work disability following diagnosis and treatment. Returning to paid employment presents evident challenges due to uncertainties regarding work ability, perceived employer discrimination, and a lack of support, thereby risking social exclusion. However, interventions addressing return to paid employment among unemployed and/or work-disabled cancer survivors are scarce. Here, we describe the protocol of a randomized controlled trial (RCT), including a process and economic evaluation, evaluating the effectiveness and cost-effectiveness of the PLACES (unemPLoyed cAnCEr survivors Support) intervention aimed at supporting unemployed and/or work-disabled cancer survivors returning to paid employment.

**Methods:**

A two-armed RCT with a 12-month follow-up period will be conducted. Eligible participants: (1) are of working age (18–65 years), (2) are diagnosed with cancer between 6 months and 10 years ago, (3) are unemployed and/or partially or fully work-disabled, (4) have completed cancer treatment, and (5) are seeking paid employment and are motivated to initiate work immediately. Participants will primarily be identified through the Dutch Social Security Agency and the Netherlands Cancer Registry and recruited via healthcare professionals. Participants randomly allocated to the intervention group (*n* = 82) will receive the PLACES intervention: a tailored supported employment intervention based on the principles of Individual Placement and Support (IPS). This includes support in seeking, returning to, and maintaining paid employment. Participants allocated to the control group (*n* = 82) will receive care as usual. All participants will be asked to complete questionnaires, at baseline (T0), and after 3 (T1), 6 (T2), and 12 (T3) months of follow-up. The primary outcome is paid employment [yes/no]. Secondary outcomes are time until paid employment, change in working hours, work ability, quality of (working) life, and self-efficacy regarding return to work. Additionally, process and economic evaluations will be conducted.

**Discussion:**

We hypothesize that the PLACES intervention will be effective in obtaining paid employment, enhancing work ability, and improving quality of life. In addition, we expect the intervention to be cost-effective. If proven effective and cost-effective, actions should be taken to implement the intervention in usual care.

**Trial registration:**

NCT06028048.

**Supplementary Information:**

The online version contains supplementary material available at 10.1186/s13063-024-08441-x.

## Background

Nearly half of the 128,000 cancer diagnoses in the Netherlands in 2023 were among the working-age population (18–65 years) [1]. Advances in cancer screening, detection, and treatment have contributed to an increase in the number of cancer survivors [1–3]. Rising survival rates and an extended retirement age have led to and will contribute to substantial growth in the number of cancer survivors in the workforce. Both the diagnosis and treatment of cancer can substantially affect work participation of cancer survivors [4]. In several prospective studies, the risk of adverse work outcomes, such as unemployment and work disability, after cancer has been indicated. On average, 64% of cancer survivors return to work (RTW), indicating that about one third of survivors experience unemployment and/or partial or full work disability [5–10]. Notably, cancer survivors are 1.4 times more likely to experience unemployment than individuals without a history of cancer [8], and this specific increased risk persists even 10 years after diagnosis [11]. This not only has a profound personal impact on cancer survivors but also societal economic consequences (e.g., [4, 8, 11, 12]).

Many cancer survivors find themselves compelled to resume their work or re-enter the labor market due to financial concerns [13] ([name] et al. in preparation). Depending on country-specific legislation concerning work and sickness absence [14], individuals with an employment contract often have the opportunity to gradually increase their work tasks and working hours and develop new skills, which can boost their confidence and facilitate adaptation to their potentially changed circumstances [15]. In contrast, cancer survivors without an employment contract lack such opportunities and face additional challenges [15, 16]. That is, factors, such as uncertainty about their ability to work, lack of support from employers or colleagues, and perceived employer discrimination when applying for a new job, contribute to potentially more difficulties when re-entering the labor market ([name] et al. in preparation) [17]. Furthermore, socio-economically disadvantaged individuals, including those with lower education levels and income, tend to participate less in rehabilitation programs and report more unmet needs in the physical, emotional, work-related, and financial area [12]. Consequently, due to a cancer diagnosis, existing social inequalities may amplify, imposing a double burden on survivors who must navigate both health-related and work-related hardships after their cancer diagnosis and treatment [12].

Over the past decades, various interventions have been developed to support employed cancer survivors in returning to or maintaining their work [18]. However, interventions aimed at supporting unemployed cancer survivors are scarce, and there is limited evidence of their effectiveness [19]. As cancer survivors without paid employment experience distinct challenges [17], it is important to tailor interventions by addressing the specific needs of this particularly vulnerable group. In a systematic review of the limited number of interventions available for unemployed cancer survivors, it has been demonstrated that the effectiveness of these interventions is associated with the integration of job search, job placement, and workplace-focused components [19]. Supported employment is an example of an intervention that combines job search and placement assistance with workplace support, aiming to help unemployed individuals secure paid employment [20, 21]. A well-defined and studied form of supported employment is “Individual Placement and Support” (IPS) [21, 22], in which individuals are first placed in suitable employment, and then provided with workplace support. IPS has consistently proven to be effective for employment re-entry in various vulnerable patient groups, including those with severe mental illnesses and spinal cord injuries [23–25].

By combining IPS principles and already proven effective intervention components [19], we developed the PLACES (unemPLoyed cAnCEr survivors Support) intervention. In a randomized controlled trial (RCT), we will evaluate the following: (1) the PLACES intervention’s effectiveness on return to paid employment compared to care as usual (CAU) and (2) its cost-effectiveness. In this paper, we provide a comprehensive description of the PLACES intervention, and the description of an RCT protocol, including a process and economic evaluation.

## Methods

A two-armed RCT will be conducted, in which participants will be randomly allocated to (1) the PLACES intervention group or (2) the CAU control group. Participant recruitment, intervention delivery, and measurement timing are shown in Fig. 1. Participants will receive questionnaires at baseline (T0) and after 3 (T1), 6 (T2), and 12 months (T3) follow-up. The participant flowchart is shown in Fig. 2. The “Standard Protocol Items: Recommendations for Interventional Trials” (SPIRIT) 2013 statement was used to structure the design of this study [26] (Appendix S1). In addition to the trial registration (NCT06028048), all items of the World Health Organization Trial Registration Data Set are outlined in Appendix S2.

**Fig. 1 Fig1:**
[figure not shown]
A schedule of enrolment, intervention allocation, and delivery of the intervention and assessments

**Fig. 2 Fig2:**
[figure not shown]
Overview of the study procedures

### Context

The study will be performed in the Netherlands, where the Social Security Agency (SSA) has two key responsibilities: (1) to determine the work ability of individuals and provide social benefits accordingly and (2) to facilitate reintegration trajectories to support individuals with re-entering the labor market after a period of absence. The type of social benefit an individual receives from the SSA is determined by their work ability, which is defined by their relative earning capacity. If a worker’s earning capacity is assessed as less than 35% of their previous salary, they are assigned a partial or full disability benefit. This applies to those who cannot continue their previous job or whose employment contract ends within the first 2 years of sick leave. The reintegration trajectories that the SSA facilitates are approved by labor experts based on the social benefit situation of individuals. The trajectories are provided on an individual basis, ensuring that they align with the specific needs and abilities of the individual.

### Participants and recruitment

Cancer survivors will be eligible to participate in this study if they:Are of working age (18–65 years);Were diagnosed with cancer between 6 months and 10 years ago;Are currently unemployed and sick-listed and/or either partially or fully work-disabled;Have completed primary cancer treatment (except long-term treatment such as hormone therapy);Are currently seeking paid employment and motivated to initiate work immediately;Are eligible for a reintegration trajectory at the SSA, based on their social benefit.

Cancer survivors who cannot speak, read, or understand Dutch and those who are diagnosed with basal cell carcinoma or a benign tumor will be excluded from participation.

Cancer survivors will be invited via three different routes (Fig. 2):Hospital route: After identification via the Netherlands Cancer Registry (on items such as diagnosis, time since diagnosis and age), recruitment occurs by treating physicians in participating hospitals, who will provide an invitation package containing a flyer, information letter, contact form, and return envelope to cancer survivors who seem eligible based on information in their medical records (e.g., treatment and work-related information registered).SSA route: Professionals from the SSA will provide the same invitation package to clients who disclose their cancer diagnosis to them (i.e., clients are not obligated to do so) and are motivated to initiate work immediately.Other route: Digital invitations will be sent to cancer survivors through various channels including Kanker.nl (a Dutch online cancer platform), the Dutch Federation of Cancer Patient Organizations, and social media.

Invited cancer survivors have the option to respond by completing a digital (using a QR code) or hard copy (using a return envelope) contact form. They can express their interest in participating or provide a reason for nonparticipation. A researcher will contact interested cancer survivors by phone, providing further information about the study and screening for eligibility criteria 1 to 5. Eligible and willing cancer survivors will be referred to the SSA’s labor expert to determine eligibility for a reintegration trajectory (i.e., inclusion criterion 6). When the SSA confirms eligibility, the cancer survivor will receive an informed consent form via email or post (with return envelope), based on their preference. A model consent form is provided in Appendix S3.

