**Primary outcome measure**			
Paid employment	1	Whether participant has engaged in paid employment since the last questionnaire [yes/no]	Dichotomous

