### Primary outcome measure

The primary outcome measure of this study is paid employment [yes/no] at any point during the 12-month follow-up. Participants will be asked at T1–T3 whether they have worked in paid employment since the previous questionnaire.

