### Effect evaluation

To evaluate the effectiveness of the PLACES intervention compared to CAU at different time points, mixed-effect regression (either linear or logistic regression) with participant as a random intercept will be conducted. Since we stratified for “received social benefit” and the “labor region,” they will be included as covariates in the model. In all models, the main independent variable will be group allocation (i.e., intervention or control group), and both unadjusted and adjusted models will be presented. Additionally, the influence of time (T1, T2, T3) on the intervention’s effect will be examined (group*time interaction effect). The adjusted models will include potential confounders, such as age, gender, time since diagnosis, type of cancer, type of treatment, importance of work, RTW expectation [15, 38], and baseline value of the dependent variable.

In addition, subgroup analyses will be performed for gender (i.e., male, female or other) time since diagnosis (i.e., ≤ 3 years, > 3 years), type of cancer diagnosis (i.e., breast, colon or other), and type of treatment (i.e., locoregional therapy, systemic therapy or multimodal treatment). All analyses will be performed on an intention-to-treat basis. Per-protocol analyses will be carried out comparing participants in the intervention group who completed at least phase 1 of the intervention and had at least one meeting in phase 2 of the intervention, to participants in the control group.

We will use mixed-effects logistic regression to assess the primary outcome, paid employment [yes/no] at T1, T2, and T3. Odds ratios (ORs) with corresponding 95% confidence intervals (CIs) will be calculated to examine the effect of the intervention on the odds of paid employment.

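### The primary outcome counts any paid work since the last questionnaire, so paid hours already held at baseline would score as success, and no eligibility criterion states that there are none

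*Protocol article*

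**What the plan says.** **Eligibility.** In Participants and recruitment, criterion 3 requires that participants "Are currently unemployed and sick-listed and/or either partially or fully work-disabled". The Abstract gives the same criterion as people who "are unemployed and/or partially or fully work-disabled". Criterion 5 adds "Are currently seeking paid employment and motivated to initiate work immediately", and criterion 6 requires eligibility for a reintegration trajectory at the Social Security Agency (SSA). The exclusions concern command of Dutch and tumour type ("those who are diagnosed with basal cell carcinoma or a benign tumor will be excluded from participation"). Current paid work is not among them.

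**Primary outcome.** The section Primary outcome measure defines it as "paid employment [yes/no] at any point during the 12-month follow-up", and at T1 to T3 asks participants "whether they have worked in paid employment since the previous questionnaire". Table 2 words the item in the same way. Neither place says that the job must be new or must have begun after randomisation.

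**Neighbouring text.** Under Secondary outcome measures, time until paid employment runs from randomisation and uses the start date of the new job. Strengths and limitations describes the primary outcome as employment obtained, and matches it to the core-outcome item on the proportion of absent workers who return to work.

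**The concern.** The eligibility rule and the outcome question are each reasonable alone but leave a gap together. Under Context, disability benefit depends on relative earning capacity, not on having no job, so a partial benefit is compatible with some paid hours. A participant with a few paid hours at T0 who wants another job, and who keeps those hours, would truthfully answer yes at T1 in either arm, whether or not the intervention did anything.

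Such a person is a primary success without having obtained work. Unless a new job follows, the time outcome has no event for the same person. Successes of this kind raise the rate in both arms, shrink the difference and the odds ratio, and cost power. The planning rates come from a study of unemployed patients (Sample size calculation), so the sample size makes no allowance for this.

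**Working it through.** **Inputs from the protocol article.** Rates 30.8% and 10.5%, power 80%, alpha 0.05, 148 evaluable and 164 enrolled (Sample size calculation); two-sided testing (end of the statistical analysis text); 1:1 allocation (Randomization), hence 74 evaluable per arm.

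**Step 1: the plan's own figure.** With the rates rounded to 31% and 11% (difference 0.20, mean 0.21), the pooled-variance formula gives

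n' = [1.96·√(2·0.21·0.79) + 0.8416·√(0.31·0.69 + 0.11·0.89)]² / 0.20² = 63.9 per arm.

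The continuity correction gives

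n = (n'/4)·[1 + √(1 + 4/(n'·0.20))]² = 73.6, so 74 per arm and 148 in total.

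Then 148/0.9 = 164.4, stated as 164. The rounding and the correction are inferred because they reproduce 148; the article does not state them. The sample size is sound on its own terms, with nobody counted as a success from a job held at baseline.

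**Step 2: dilution.** Let f be the share in each arm with paid hours at T0 who keep them, and so answer yes. If the others obtain work at the planning rate p, the observed rate is f + (1 − f)p and the difference shrinks by the factor (1 − f). The article does not give f, so the values below are assumptions. Power is for an uncorrected two-sided chi-square test at 74 per arm, by exact enumeration of two binomials.

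| f (assumed) | Intervention | Control | Difference (points) | OR | Power |
|---|---|---|---|---|---|
| 0 | 30.8% | 10.5% | 20.3 | 3.79 | 0.881 |
| 3% | 32.9% | 13.2% | 19.7 | 3.22 | 0.826 |
| 5% | 34.3% | 15.0% | 19.3 | 2.96 | 0.789 |
| 10% | 37.7% | 19.5% | 18.3 | 2.51 | 0.703 |

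Example at f = 5%: 0.05 + 0.95·0.308 = 0.343 and 0.05 + 0.95·0.105 = 0.150; OR = (0.343/0.657)/(0.150/0.850) = 2.96.

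**Step 3: the same check by the method that reproduces 148.** With 31% and 11% and the continuity correction, power is 0.80 at f = 0, 0.70 at 5% and 0.61 at 10%. The starting level is lower and the loss is of similar size: about 10 points at 5% and just under 20 at 10%.

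The planned primary analysis is a mixed-effects logistic model over T1 to T3, so these single-comparison figures are approximate.

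**The case against.** The strongest reply is that the criteria are cumulative and, taken together, describe people without work. Criterion 5 asks for readiness to initiate work, which most naturally means not working now. Under criterion 6 an SSA labour expert must confirm eligibility for a trajectory, and Context presents these trajectories as support for re-entry after absence. The Background describes the target group as survivors without paid employment. Table 2 compares working hours over T1 to T3 only, which fits a design that expects no hours at T0. Criterion 3 can also be parsed so that being unemployed governs the whole phrase.

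Most of this stands. It makes paid work at T0 uncommon, but it does not rule it out: the Abstract's wording lets work disability qualify without unemployment, seeking a job is compatible with having a few paid hours, and the SSA's detailed rules are not shown.

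A reader might infer more than the document supports:

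- **That some participants are known to be employed at baseline, because adjusted models include the "baseline value of the dependent variable".** That phrase belongs to one generic covariate list for all outcomes and is no evidence of baseline employment.
- **That the treatment comparison is biased.** Randomisation balances these participants on average. Chance imbalance is possible, because stratification is by region and benefit type.
- **That the trial is underpowered.** This depends wholly on f. By the chi-square calculation, power is still about 0.83 at 3%.
- **That these participants have no time outcome.** One who starts a new job has a date; one who does not can be censored.

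**Conclusion.** The concern holds as a gap in the primary outcome definition. The rule as written can count an event that is not the one the trial sets out to measure, and it differs from the new-job basis of the time outcome. The consequence is dilution in both arms. With an assumed 3%, 5% or 10% holding and keeping paid hours at T0, chi-square power at 74 per arm goes from 0.88 to about 0.83, 0.79 or 0.70, and the odds ratio from 3.8 to about 3.2, 3.0 or 2.5. These figures also assume that the other participants obtain work at the planning rates. Given criteria 5 and 6 the true share is probably small, but the document gives no figure. The sample size calculation is not in error.

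**What to change.** In Primary outcome measure and in Table 2, define the primary outcome as paid employment started after randomisation. Derive it from the job start date already collected for time until paid employment. Anyone with paid hours at T0 then counts as a success only on starting a new paid job, and the primary and time outcomes rest on the same event.

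Leave the eligibility criteria as they are. Recruitment began in September 2023, minimal exclusion is a stated aim (Table 1), and the outcome wording alone removes the problem.

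The cost is a formal amendment to the primary outcome wording during the trial. No new data item is needed. The downside is that extra hours in an existing job would not count towards the primary outcome, though paid hours during follow-up are still recorded under change in working hours.

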### Sample size calculation

In a previous study of unemployed patients with spinal cord injury, participants who received IPS were significantly more likely to return to paid employment than those in the CAU group (30.8%; 95% CI 21.8–41.6 versus 10.5%; 95% CI 5.2–19.7, respectively) [25]. Based on these data, a power of 80% and an alpha of 0.05, a total of 148 cancer survivors are required to detect the same difference of 20% between the two groups (nQuery Advisor 7.0). Accounting for a 10% loss to follow-up, we aim to include 164 cancer survivors.

### Randomization

Participants will be randomly allocated to either the intervention or CAU control group (1:1), using Castor EDC [27], stratified according to region in the Netherlands and social benefit type. The allocation sequence will be generated by the executing researcher ([name]) in Castor EDC. The sequence is concealed for everyone until participants are allocated. Neither the participant nor the research team and those delivering the intervention will be blinded to the randomization.

### The PLACES intervention

#### Development

The PLACES intervention is a supported employment program, guided by trained and certified IPS coaches. The program was based on established principles of IPS (Table 1), which have proven effective in various other populations [23–25], with higher adherence to these principles leading to a more effective intervention [28]. Staying true to IPS principles was the foundation for the development of the PLACES intervention. Nevertheless, adjustments to three principles were necessary. Firstly, *zero exclusion* was not feasible due to funding structures within the SSA, and we recognized that cancer treatment is highly invasive, making it unrealistic for cancer survivors undergoing treatment to begin a new paid job (thereby excluding those still in treatment). To mitigate exclusion, we minimized the number of both inclusion and exclusion criteria. Additionally, *integration of rehabilitation and the healthcare system* is not yet possible. The PLACES intervention cannot be integrated into the oncological healthcare system since rehabilitation and oncological healthcare in the Netherlands are not yet adequately interconnected, unlike the more integrated approach seen in mental healthcare. Lastly, we could not guarantee *time-unlimited support* due to restrictions from the SSA and the duration of the study. The operationalization of the IPS principles for the PLACES intervention is shown in Table 1.

**Table 1 Tab1:** Operationalization of the IPS principles for the PLACES intervention

Principle	Operationalization
Focus on competitive employment	The focus is on finding competitive employment in the community rather than volunteering or sheltered work for persons with disabilities
Eligibility based on client choice (zero exclusion)	Eligibility is based on the cancer survivor’s desire to work, rather than readiness or ability to work. Minimal exclusion is intended with exclusion criteria being: no social benefit from the SSA, unable to speak Dutch, or being diagnosed with basal cell carcinoma
Integration of rehabilitation and healthcare system	Re-turn, an organization specialized in reintegration after cancer, will train IPS coaches, equipping them with comprehensive knowledge on medical and social consequences of cancer diagnosis and treatment
Attention to worker preferences	Services will be based on each person’s preferences and choices, rather than the coaches’ or employer’s judgments. This means that preferences for work of the cancer survivor will guide the job search, rather than availability of existing jobs
Personalized benefits counseling	The IPS coach will help cancer survivors obtain personalized, understandable, and accurate information about their social security situation
Rapid job search	The cancer survivor will actively engage in job search and job development activities with their IPS coach, rather than conducting pre-vocational assessment or work readiness activities. The aim is to contact a potential employer within 30 days of the initial meeting
Systematic Job Development	Services will take place in a real-world setting. The IPS coach is expected to assist with finding a suitable workplace and providing the necessary “on the job” support
Time-unlimited and individualized support	Follow-along support will be provided by the IPS coach for 1 year, to support job maintenance

In addition to these organizational adjustments of the IPS principles, the content of the PLACES intervention was tailored to the needs and preferences of unemployed and/or work-disabled cancer survivors. This was based on a systematic review [19] and focus group interviews ([name] et al. in preparation) with cancer survivors who had engaged in job-seeking activities for paid employment in the 2 years prior to the study (from a situation of unemployment or work disability). The review on interventions aimed at enhancing the work participation of cancer survivors [19], advocated, among others, for inclusion of the workplace even for individuals without an employment contract who are re-entering the labor market. This is in line with the principles of IPS on systematic job development and time-unlimited individualized support and resulted in the emphasis of support on the job and involvement of the employer during the intervention. The focus group interviews provided insight into facilitators and barriers encountered during the process of reintegration after cancer as well as the cancer survivors’ met and unmet needs throughout the reintegration process ([name] et al. in preparation). The insights gained from these interviews were used to formulate explicit recommendations for the coaches who perform the intervention, such as guidelines regarding the frequency and nature of the meetings. The specific guidelines for each phase of the intervention can be found in the content of the intervention and Fig. 3.

